***Sociodemographic & medical data***								
Date of birth	+							
Sex	+							
Participant personal data	+							
GP information data	+							
Date, hour and location of fall	+							
Fall circumstances and consequences	+							
Legal protection measures	+							
Education level	+		+					
Life style (living alone or with a partner, family, etc.)		+						
Domestic aid			+					
Medical history		+						
Fall history in the last 12 months		+						
Medical and non-medical treatments		+						
Number of hospitalisations in the last 6 months			+					
***Outcome data***								
Death				+	+	+	+	+
Institutionalisation				+	+	+	+	+
Hospitalisations				+	+	+	+	+
Additional EMS calls relating to a fall^a^				+	+	+	+	+
ADL [34]			+		+		+	
EQ-5D-5L [36, 37]			+		+		+	

*GP* General Practitioner, *CRA* clinical research associate, Investing investigator, *ADL* activities of daily living, EQ-5D-5L EuroQol-5 Dimension-5 levels, M0, M6, M12, M18, M24 match months 0, 6, 12, 18 and 24 respectively from the enrolment (t0) till the end of the follow-up period. ^a^additional EMS calls relating to a fall are collected via the Regional Emergency Department Observatory of Occitanie. ^b^Data on death, hospitalisation and institutionalisation and additional EMS calls are collected by the CRA (M6, M12, M18 and M24) and every six months until the end of the follow-up period of the last enrolled subject

**Table 4 Tab4:** Participant data collection timeline throughout calls and visit assessments (continued on next page)

	Nurse Visit 0	Nurse Visit 1	Nurse call 2	Nurse call 3	Nurse Visit 2	Nurse call 4	Nurse Visit 3	Nurse call 5	Nurse Visit 4	Nurse call 6	Nurse Visit 5
	≤ 14 d	≤ 30 d	M2	M4	M6	M9	M12	M15	M18	M21	M24
***Socio-demographic and medical data checking***											
Participant contact information checking (address and phone number)	+		+	+	+	+	+	+	+	+	+
Participant's family, legal representative or trusted person contact information checking	+		+	+	+	+	+	+	+	+	+
Legal protection measures checking	+		+	+	+	+	+	+	+	+	+
General Practitioner information data checking	+		+	+	+	+	+	+	+	+	+
Life style checking (living alone or with a partner, family, etc.)	+		+	+	+	+	+	+	+	+	+
Domestic aid checking	+		+	+	+	+	+	+	+	+	+
Medical history checking	+		+	+	+	+	+	+	+	+	+
Pharmacological and non-pharmacological treatments	+		+	+	+	+	+	+	+	+	+
Hospitalisation history from the last contact	+		+	+	+	+	+	+	+	+	+
***Standardised geriatric assessment***											
Body weight and body mass index	+				+		+		+		+
MMSE [38]	+				+		+		+		+
Mini-GDS [39]	+				+		+		+		+
ADL [34]	+				+		+		+		+
IADL [40]	+				+		+		+		+
Fried criteria [33]	+						+				+
SPPB [41]	+						+				+
MNA [42]	+				+		+		+		+
Alcohol consumption	+				+		+		+		+
***Fall record***											
Fall from the last contact	+		+	+	+	+	+	+	+	+	+
Blood pressure	+				+		+		+		+
Check for orthostatic hypotension	+				+		+		+		+
One-leg balance [43]	+				+		+		+		+
Foot examination	+				+		+		+		+
Sensorial assessment	+				+		+		+		+
Amsler Grid [44]	+				+		+		+		+
Pain survey: localisation and intensity	+				+		+		+		+
Sleep survey: sleeping disorders, tiredness upon waking, drowsy episodes during the day, night awakenings	+				+		+		+		+
Environment evaluation: type of habitat, housing occupation status environmental hazards, planned improvements	+				+		+		+		+
Technical walking aid use checking	+				+		+		+		+
Risk taking	+				+		+		+		+
***Summary data and monitoring***											
Monitoring of therapeutic changes					+		+		+		+
Compliance / difficulty of medication intake	+		+	+	+	+	+	+	+	+	+
Emerging of new events (pathologies, social, etc.)		+	+	+	+	+	+	+	+	+	+
PIP presentation and application mode		+	+	+	+	+	+	+	+	+	+
Adherence to recommendations		+	+	+	+	+	+	+	+	+	+
Primary care physician frequentation			+	+	+	+	+	+	+	+	+
Other specialist consultation			+	+	+	+	+	+	+	+	+

*GP* General Practitioner, *d* day, *M* month, *MMSE* Mini Mental State Examination, *Mini-GDS* Mini Geriatric Depression Scale, *SPPB* Short Physical Performance Battery, *ADL* Activities of daily living, *IADL* Instrumental Activities of Daily Living, *MNA* Mini Nutritional Assessment, *PIP* Personalised Intervention care Plan. Nurse visit 0 and 1 should be done within a maximum of 14 days and 30 days after enrolment. M2, M4, M6, M9, M12, M15, M18, M21 and M24 match months 2, 4, 6, 9, 12, 15, 18 and 24 respectively from the enrolment till the end of the follow-up period

### Experimental design

An intervention includes three main actions: (*i*) CGA [35] and fall risk factor assessment, (*ii*) PIP to address potentially reversible and modifiable factors and (*iii*) patient follow-up by an experienced geriatric nurse over the 24-month follow-up period (Table 2).

(*i*) The CGA is performed during the first nurse visit at the participant’s home (V0) within a maximum of 14 days from the date of the EMS intervention. In addition, a fall record is performed to track potential risk factors (*e.g*. sensorial assessment, one-leg balance [43], Amsler grid [44], environmental hazards, etc.). Details on performed assessments and data collected throughout the nurse home visit are provided in Table 4.

(*ii*) A PIP is established throughout a Multidisciplinary Team Meeting (MDTM) within a maximum of 10 days following the first nurse visit. The geriatrician investigator, the nurse and the hospital pharmacist participate in this meeting to discuss the clinical and social status of the participant and suggest appropriate solutions regarding possible warning signs.

The PIP is proposed according to emphasis on preventing falls, standard geriatric recommendations [45], medical treatment adjustment and takes into account the patient's desires and concerns. It is discussed and approved beforehand by the participant’s GP and then given to the participant during the nurse visit at home within 10 days after the MDTM (V1). A maximum of three recommendations are proposed to the participants to maximise their adherence. For instance, prescription of physically adapted activities, attending of equilibrium and fall prevention workshops offered by the municipality, nutrition education, medication review carried out in a primary care setting, etc. The inclusion of the GP in the proposed intervention program should ensure patient adherence and compliance.

During the next four visits (V2, V3, V4, V5) every 6 months, the nurse re-evaluates the patient and ensures the effective application of the PIP or reports the possible blocking points. Relevant points are addressed after each visit to the participant’s GP. In addition, five nurse phone calls are scheduled at 2, 4, 9, 15 and 21 months (Fig. 1) in order to keep in touch with the participant and follow the PIP application.

In case of a health crisis and/or if it is impossible for the nurse to visit the participant’s home, the nurse can exceptionally perform a remote screening via video call or telephone if the subject does not have the necessary IT equipment or is unable to use it.

## Outcomes

Primary and secondary outcome data are collected by CRA phone calls twice a year throughout the study. The CRA is blind of the participant group. The end of the patients’ follow-up matches the end of the follow-up of the last enrolled participant. This means that the first enrolled participant has 54 months of follow-up (compared to 24 months for the last enrolled participant). In case of difficulty of reaching the elderly, the CRA contacts: 1- the patient’s close relatives or legal representative and 2- the participant’s GP in order to collect outcome measures.

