### Inclusion and exclusion criteria and recruitment procedure

During the recruitment phase, the ORU-Occitanie makes available to the CRA and investigators participating in this study (via its secured digital professional platform) a daily read-only listing of subjects over 70 years old who have called the EMS because of a fall issue. Calls are automatically screened according to the following key words: fall, fell, fracture, lift, lifted, lifting, on the ground and slipped.

The CRA of each hospital centre is in charge of selecting subjects in his/her territory and ensures that the selected subjects meet the inclusion and exclusion criteria listed in Table 1. Subjects with cognitive and hearing impairments or other disorders are not excluded if they have close relatives or a legal representative able to give consistent phone information. Subjects can be included in the study regardless of the interventions already underway even if they are related to falls prevention. However, subjects with activities of daily living (ADL) set to 0 are excluded, given that PIP intervention would not be appropriate.

**Table 1 Tab1:** RISING-DOM inclusion and non-inclusion criteria

Inclusion criteria	Exclusion criteria
Age ≥ 70 years	Total dependency (ADL at 0)
Living at home	Entry into a nursing home already scheduled in the next 3 months
Living at maximum 45 min from a hospital centre participating in the study (for logistical reasons)	Subject already enrolled in this study
Intervention of the EMS for a fall at home without there being hospitalisation or with hospitalisation less than 24 h	
Participant (close relatives or legal representative) able to give phone information	
Participant (close relatives or legal representative) has given its consent for participation in the study	
Participant affiliated to a social security scheme	

*EMS* emergency medical service, *ADL* activities of daily living [34]

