### Data collection procedure and randomisation

During the phone call, prior to the enrolment of each participant, the investigator collects information related to the patient’s medical history, his/her current list of pharmacological and non-pharmacological treatment, his/her lifestyle and previous history of falls.

After study recruitment and collection of baseline data, each participant is randomly allocated (1:1) to either the intervention or control arm. Blocked randomisation with random block sizes will be performed. The randomisation will be stratified according to lifestyle (living alone versus living with one’s relatives) and the existence or not of a history of a fall in the previous 12 months and the site.

Data on outcomes (death, hospitalisations, institutionalisation and number of additional EMS calls relating to falls) are collected prospectively by the CRA at 6, 12, 18 and 24 months (M6, M12, M18 and M24 respectively) of the patient’s follow-up and then every six months until the end of the study for both groups. The Activities of Daily Living (ADL) [34] and quality of life (EQ-5D-5L) [36, 37] scales are collected by the CRA once a year at inclusion, 12 and 24 months of follow-up. The exhaustive list of the variables collected by the CRA during the RISING-DOM study for all patients (intervention and control group) is summarised in Table 3. For both groups, a log-book is given to the participants to prospectively collect the events occurring during the follow-up period such as falls, hospitalisations and other side effects with their date. This aims to help the CRA collect with precision the occurrence of events. This document is not accessed/collected by the study team and it works simply as a memory aid. Data collected during nurse home visits (six visits) and nurse phone calls (five phone calls) for the “intervention group” are listed in Table 4.

**Table 3 Tab3:** RISING-DOM data and timeline collection and for ‘intervention group’ and ‘usual-care control group

	CRA call	Investing call	CRA calls					
		Enrolment allocation	Baseline assessment	Follow-up assessment				
	-t1	t0	M0	M6	M12	M18	M24	^b^
Screening for eligibility	+	+						

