**Quality of life assessment**
The EuroQol-5 Dimension-5 levels (EQ-5D-5L) is a generic tool to measure the health-related quality of life on five dimensions (mobility, self-care, usual activities, pain/discomfort and anxiety/depression) [36, 37]. Patients are also asked to give a score out of 100 about their global quality of life (health analogue scale).

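### The fallback to relatives and then the GP is not limited to dated events, so as printed it also covers EQ-5D-5L and ADL, where the rater can change and, in the intervention arm, may be the GP who approved the care plan

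*Protocol article*

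**What the plan says.** The Outcomes section opens with its scope: "Primary and secondary outcome data are collected by CRA phone calls twice a year throughout the study". The same paragraph then gives one fallback for participants who are difficult to reach, in two steps: "the patient’s close relatives or legal representative and 2- the participant’s GP in order to collect outcome measures". No outcome is excepted.

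ADL and EQ-5D-5L are within that scope. Table 3 lists both under outcome data, the Secondary outcomes section defines both, and under Data collection procedure and randomisation the two "scales are collected by the CRA once a year at inclusion, 12 and 24 months of follow-up". For the 0–100 health scale the article says: "Patients are also asked to give a score out of 100 about their global quality of life".

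Two other statements bear on who answers:
- The recruitment section admits some participants through an informant from the start: "Subjects with cognitive and hearing impairments or other disorders are not excluded if they have close relatives or a legal representative" able to give consistent information by phone.
- Under Experimental design, the GP has a part in the personalised plan (PIP): "It is discussed and approved beforehand by the participant’s GP". The GP is also sent relevant points after the nurse's follow-up visits. Both apply to the intervention arm only.

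Under Secondary outcomes analysis, ADL and EQ-5D-5L at 24 months are compared by linear models adjusted for stratification factors, age and, if appropriate, the score at inclusion. The respondent is not among the covariates named.

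**The concern.** A substitute informant can report a fact but cannot stand in for a self-rating without changing what is measured. Whether someone has died, entered a nursing home or been in hospital does not depend on who is asked. A 0–100 rating of one's own health does, and an ADL score may.

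Under the rule as printed, one participant could answer at M0, a relative at M12 and the GP at M24, and the M24 score would enter the model as the same measure. Adjusting for the M0 score cannot separate a change of rater from a change in health.

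Two features could make this differ by arm. First, Table 4 has nurses recheck the contact details of the participant and family at 10 of 11 scheduled contacts in the intervention arm; controls have no nurse contacts. Direct reachability, and so the respondent mix at M24, may therefore differ. Second, a GP who answers for an intervention participant has approved that participant's plan and knows the allocation, while a control participant's GP has no such role. Blinding the CRA who makes the call does not remove the involvement of the person answering.

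At stake are the 24-month comparisons of quality of life and functional dependency, not the primary result.

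**Working it through.** **1. What is not affected.** The only stated design figure is the event count for the primary log-rank test.
- Hazard ratio from the stated rates: 18% × 0.70 = 12.6%; ln(1 − 0.126) / ln(1 − 0.18) = 0.679, as stated.
- Events by Schoenfeld's formula: 4 × (1.960 + 0.842)² / (ln 0.679)² ≈ 210, against the stated 211. With 211 events the power is 80.3%.

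The figure is reproduced. It rests on deaths and institutionalisations, for which a relative or GP is a suitable source, so nothing here changes it.

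**2. Outcome by outcome.**

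| Outcome | Nature | Is a relative or GP adequate? |
|---|---|---|
| Death, institutionalisation, hospitalisation | dated event | yes |
| Additional EMS calls | dated event, mainly from the regional platform | yes, as a check |
| ADL | rated score | relative possible; GP brings an arm-specific role |
| EQ-5D-5L with 0–100 scale | rating asked of the patient | relative only as a declared proxy; GP no |

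**3. How bias would arise.** Let g be the mean gap between a substitute's score and the participant's own, and p_I and p_C the shares of substitute-rated scores at M24 in the intervention and control arms.
- Gap common to both arms: bias (intervention − control) = g × (p_I − p_C). This is zero when p_I = p_C.
- Gap that differs by arm, as it could for GPs: bias = p_I g_I − p_C g_C. With equal shares p this is p × (g_I − g_C), which need not be zero.

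**4. Illustration.** Every input below is assumed; the article gives none of them.
- Substitutes 10 points lower, 20% intervention against 30% control: −10 × (0.20 − 0.30) = +1.0 point.
- Substitutes 15 points lower, 20% against 35%: −15 × (0.20 − 0.35) = +2.25 points.
- If substitutes rate higher, or substitution is commoner in the intervention arm, the sign reverses.

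In SD units, with 300 assessed per arm, SE = √(2/300) = 0.0816. The two-sided type I error is 1 − Φ(1.96 − b/SE) + Φ(−1.96 − b/SE), with b the bias:

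| Substitutes lower by | 20% v 20% | 30% v 20% | 40% v 20% |
|---|---|---|---|
| 0.2 SD | b = 0; 5.0% | b = 0.02; 5.7% | b = 0.04; 7.8% |
| 0.3 SD | b = 0; 5.0% | b = 0.03; 6.6% | b = 0.06; 11.4% |
| 0.5 SD | b = 0; 5.0% | b = 0.05; 9.4% | b = 0.10; 23.2% |

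Columns give the control share against the intervention share. The range starts at no bias, and the document does not say where in it the trial lies.

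**The case against.** **A narrower reading.** The Outcomes paragraph speaks of calls twice a year, whereas the scales are collected yearly. The data collection section, when it speaks of outcomes gathered every six months, lists only events and treats ADL and EQ-5D-5L separately as scales. The fallback may thus be meant for events alone, and nowhere does the article say that a GP scores a scale. This reading is possible but not the plain one, because the paragraph names secondary outcomes and Table 3 counts both scales as outcome data. The fair statement is that the rule permits GP scoring, not that it prescribes it.

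**Detail an article omits.** Proxy forms, a respondent field and respondent analyses may stand in the full protocol or analysis plan. Agreed: their absence here is no fault. The point is the unrestricted rule that is printed.

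**Proxies need not be common.** A reader might infer that they will be, from the pilot's 58% with MMSE ≤ 24. That figure comes from 91 people and shows neither that they were unreachable nor that they could not rate themselves. Informants for impaired participants come from the recruitment rule, which is a separate and deliberate choice.

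**Differential decline.** A reader might infer that an intervention which slows decline would produce a spurious benefit through the rater mix. If decline truly differs, there is a true effect, and a shift of raters that follows from it distorts its size rather than creating it. Under no effect, a difference in reachability or an arm-specific rater gap would be needed; both are plausible, and neither is shown.

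**Blinding.** The trial is open and participants know their arm, so self-ratings are unblinded too. What remains of the GP point is the change of rater and the role held in one arm only. The GP is also the last resort, with no frequency given.

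**Conclusion.** The concern holds for the two rated secondary scales. As printed, the fallback lets the respondent for EQ-5D-5L and ADL change between M0 and M24, and lets a GP with an arm-specific role give the scores. The stated models cannot separate rater change from health change.

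The size and direction are unknown. The illustrative 1.0 to 2.25 points, and type I error of 5% to 23%, rest wholly on assumed gaps, shares and numbers assessed. They should not be read as an estimate, nor as evidence that the trial favours the intervention. With a rater gap common to both arms and an equal respondent mix there is no bias from this source.

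The primary endpoint, the 211 events, and the use of relatives and GPs for dated events are sound on this point. The conclusion assumes that the Outcomes paragraph means what it says when it includes secondary outcomes.

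**What to change.** - **Outcomes section:** limit the GP fallback to death, institutionalisation, hospitalisations and EMS calls.
- **EQ-5D-5L and ADL:** accept only the participant or, where needed, a relative or legal representative, with the proxy wording of EQ-5D-5L, and preferably the same respondent throughout. Excluding relatives altogether, or strictly fixing the respondent at M0, would go too far: it trades rater inconsistency for missing data.
- **e-CRF:** record who answered at each remaining M0, M12 and M24 call. If this is not recorded, no later analysis can separate self-rated from third-party scores.
- **Secondary outcomes analysis:** add a sensitivity analysis restricted to participants with the same respondent at M0 and M24.

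The cost is one e-CRF field, the proxy form of an instrument already in use, and one extra analysis. The downside is a few more missing scale scores where only the GP can be reached; the document does not allow their number to be estimated. Because inclusion began in October 2019, the M0 respondent may be unknown for participants already enrolled, and the sensitivity analysis may not be able to include them.

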### Primary outcome

The primary outcome in this study is time to institutionalisation or death (before institutionalisation) in both groups (first occurring event). It is a composite criterion that consists of the period (days) between the enrolment (t0) until the onset of institutionalisation or death before institutionalisation and that is collected every 6 months. It is considered as an appropriate indicator of the intervention efficiency for the target population based on our pilot feasibility study.

### Secondary outcomes

Secondary outcomes are collected at inclusion, 12 and 24 months follow-up and are as follows:
**Functional dependency level**
The ADL scale is commonly used to assess basic functional capacities [34]. The scale stands on a score of 6 related to the execution of basic tasks of daily living (bathing, dressing, using the toilet, getting into or out of a bed or chair, faecal and urinary continence and eating).
**Quality of life assessment**
The EuroQol-5 Dimension-5 levels (EQ-5D-5L) is a generic tool to measure the health-related quality of life on five dimensions (mobility, self-care, usual activities, pain/discomfort and anxiety/depression) [36, 37]. Patients are also asked to give a score out of 100 about their global quality of life (health analogue scale).
**Rate of additional EMS calls relating to a fall over 24 months**
These data are collected from the ORU-Occitanie platform and verified during the CRA follow-up phone calls.
**Time before occurrence of the first additional EMS call relating to a fall**
This represents the time between the first fall recorded at enrolment time (t0) and the occurrence of the first additional EMS call relating to a fall over 24 months.
**Unscheduled hospitalisation rate over 24 months**

**Time before occurrence of the first unscheduled hospitalisation**

**Death and institutionalisation rate over 24 months**

### Sample size

The 24-month event rate (institutionalisation or death before entering an institution) is estimated at 18% in the control arm based on available data in the literature [46]. A relative reduction of 30% is expected in the intervention arm at 24 months (Hazard Ratio = 0.679) with a two-sided test. 211 events should detect this Hazard Ratio (with a two-sided test Log-rank test) with a power of 80% and alpha risk of 0.05. With a study over 54 months, a uniform inclusion in the first 30 months and 10% of people lost to follow-up per year, it will be necessary to include 595 subjects per group to reach this number of events, thus 1,190 subjects in total.

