### Participants

Subjects enrolled in this study are over 70 years old, have fallen at home and called an EMS of the territories participating in the study during the inclusion period, without being hospitalised or hospitalised for less than 24 h. The subjects living in nursing homes are excluded from this study (Table 1).

The patient’s oral informed consent is required. However, if the patient is not able to correctly understand the information provided and/or to express his/her wishes, the oral consent should be given to the investigator by close relatives or the legal representative.

The inclusion period started in October 2019 and lasts 30 months. By the end of this period, a total of 1,190 subjects should be enrolled.

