These calls may, however, be early indicators of problems requiring comprehensive medical evaluation and follow-up [62]. The main purpose of the RISING-DOM study is to assess the effectiveness of a PIP monitored by a close nurse home follow-up on time to institutionalisation or death. The quality of life, the functional autonomy evolution, the number of unscheduled hospitalisations, number of EMS calls relating to a fall, the number of deaths and institutionalisations are also monitored as secondary outcomes. The originality of this study is to build a professional network around a poorly studied and vulnerable population to prevent institutionalisation and death, and help to define the best approach for fall management based on home health care continuity. Our research network covers rural, as well as urban and semi-urban communities. If this protocol and the new organisation proposition reveal their efficiency, it could be easily generalised to other regions. During the first COVID-19-related national lockdown, (from 17 March 2020 to 11 May 2020), planned nurse home visits of follow-up (*n* = 7) have been performed remotely and have been appreciated by the elderly, as they felt isolated. However, the recruitment of new participants was interrupted in that period and has gradually resumed according to the implication of the study sites in the management of the health crisis. Consequently, we might encounter some difficulties to reach the expected sample size. In that case, a substantial modification will be submitted in a new protocol study version. The first results should be available in 2024.

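### The stated inputs give about 237 events and 84–85% power at 1,190 subjects; 211 events need only about 1,050–1,060, so 1,190 is a conservative figure and not the number required

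*Protocol article*

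**What the plan says.** All of the inputs stand in the Sample size section of the protocol article. The 24-month rate of institutionalisation or death "is estimated at 18% in the control arm based on available data in the literature". The effect is given as follows: "A relative reduction of 30% is expected in the intervention arm at 24 months (Hazard Ratio = 0.679) with a two-sided test". A target of 211 events for the log-rank test is tied to this effect, "with a power of 80% and alpha risk of 0.05". The design is described by "With a study over 54 months, a uniform inclusion in the first 30 months", with 10% of subjects lost per year. The conclusion is that "it will be necessary to include 595 subjects per group to reach this number of events, thus 1,190 subjects in total".

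Three other places bear on the point:

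- The Outcomes section confirms that follow-up runs to a common end, from 54 months for the first participant to 24 months for the last.
- The Primary outcome analysis section censors subjects at loss to follow-up, so events before loss count.
- The Participants section repeats that "a total of 1,190 subjects should be enrolled", and the Discussion warns that, after the lockdown, "we might encounter some difficulties to reach the expected sample size", in which case a substantial modification would be submitted.

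**The concern.** The paragraph gives a full set of inputs and presents 595 per group as what is needed to obtain 211 events. If the inputs imply materially more events at that size, the sentence is wrong as written, and the power expected at full enrolment is higher than a reader would suppose.

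The practical stake is modest but real. Recruitment was interrupted, and the article foresees an amendment if the planned size is not reached. A sponsor who takes 1,190 as the minimum for 80% power could misjudge what a shortfall costs.

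**Working it through.** **Step 1. Hazard ratio (reproduces).** The intervention rate at 24 months is 0.70 × 18% = 12.6%. Under exponential times the yearly hazards are:

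- control: −ln(0.82)/2 = 0.0992
- intervention: −ln(0.874)/2 = 0.0673

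The ratio is ln(0.874)/ln(0.82) = 0.679, as stated.

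**Step 2. Events (reproduces).** Schoenfeld's formula for 1:1 allocation is D = 4(1.960 + 0.842)²/[ln(0.679)]² = 31.40/0.1499 = 209.5, or 210 events against the stated 211. With 211 events the power is Φ(√211/2 × |ln 0.679| − 1.960) = 0.803. The statement that 211 events give 80% power is therefore correct.

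**Step 3. Probability of an observed event.** Take a loss hazard g = −ln(0.9) = 0.1054 per year, accrual A = 2.5 years and minimum follow-up F = 2 years. With l the event hazard and s = l + g:

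P(event) = (l/s) × [1 − (e^(−sF) − e^(−s(F+A)))/(sA)]

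- Control: s = 0.2046, so P = 0.4850 × [1 − (0.6642 − 0.3983)/(0.2046 × 2.5)] = 0.4850 × (1 − 0.5199) = 0.2328
- Intervention: s = 0.1727, so P = 0.3899 × [1 − (0.7079 − 0.4597)/(0.1727 × 2.5)] = 0.3899 × (1 − 0.5749) = 0.1657
- Mean over arms: 0.1993

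**Step 4. Events at 1,190, and subjects for 211 events (does not reproduce).**

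- Expected events at 595 per group: 595 × 0.2328 + 595 × 0.1657 = 138.5 + 98.6 = 237
- Power with 237 events: Φ(√237/2 × |ln 0.679| − 1.960) = 0.846
- Subjects for 211 events: 211/0.1993 = 1,059, about 530 per group
- Excess: 1,190 − 1,059 = 131 subjects, and 131/1,059 = 12%

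Simulating the log-rank test (4,000 trials per setting) gave 237.3 events and 84.4% power at 1,190, and 211.2 events at 1,060.

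**Step 5. Other readings of the same inputs.**

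| Variant | Subjects |
|---|---|
| 10% read as a hazard of 0.10 | 1,050 (239 events at 1,190) |
| Freedman's formula (215 events) | 1,079 |
| Lachin–Foulkes | 1,063–1,072 |
| Log-hazard variance | 1,070–1,079 |
| No loss to follow-up | 899 |
| No-loss size divided by 0.9 | 999 |

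None of these reaches 1,190.

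**Step 6. What would make 1,190 yield 211 events.** Changing one input at a time and keeping the method of step 3, any one of these suffices:

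- an annual loss of about 17%
- a control rate of about 16% at 24 months
- a minimum follow-up of 18 months in a 48-month study (about 1,193–1,202 subjects)

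The last contradicts the stated design. The first two contradict the stated rates, but either could occur in practice.

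**The case against.** The strongest reply is that a simple loss allowance does arrive at the stated figure. Mean planned follow-up under uniform accrual is (24 + 54)/2 = 39 months, or 3.25 years, and 899 × (1 + 0.10 × 3.25) = 899 × 1.325 = 1,191. Dividing 899 by one minus the expected share lost (24–25%) gives 1,187–1,204. The article condenses a fuller protocol that may describe such a step. This stands as a plausible origin, but it remains an inference, because the article states neither calculation. Nor does it rescue the sentence: the first is a rough multiplicative inflation, and the second treats lost subjects as if they contributed no events, which conflicts with censoring at loss.

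The reply also holds that the error is on the safe side. That is right: no error rate, estimand or inference is damaged.

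Several stronger readings are tempting but not supported:

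- **That the 80% power is misstated.** It is attached to 211 events, and there it is correct.
- **That only a 17% annual loss reconciles the figures.** Step 6 shows other single changes that do so.
- **That loss was counted twice.** Inflating 1,059 by a further 10% gives 1,059/0.9 = 1,176, which fits less well than 1,191.
- **That the foreseen modification will be decided on the head count.** The Discussion does not say on what basis it would be decided.
- **That about 1,060 subjects would be a safe new target.** That size has no margin if the control rate, which comes from the literature, is two points too high.

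**Conclusion.** The concern holds, limited to one step. The hazard ratio, the event target and its power are right. The claim that 1,190 subjects are needed to reach 211 events is not. Under the stated inputs, 1,190 gives about 237 expected events and about 84–85% power, and 211 events are expected from about 1,050–1,060 subjects. The trial is about 12% larger than its stated power needs, and it is not underpowered.

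This rests on exponential event and loss times, loss unrelated to outcome and equal in both arms, uniform accrual, and follow-up to the common end date. It also depends on the 18% and 10% inputs being correct, since small departures from them absorb the surplus. This is an error in a stated figure, worth correcting, with a limited consequence.

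**What to change.** In the Sample size section, and in any amendment that repeats it, take one of two courses:

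- State that 1,190 subjects give about 237 expected events and about 84% power, and that the 211 events for 80% power are expected from about 1,060 subjects.
- Keep 1,190 and describe the excess over 211 expected events as a deliberate margin.

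Either way, say how the 10% annual loss was converted into subjects, and note that the margin is used up at a control rate of about 16% or an annual loss of about 17%. The figure of 1,060 should appear as a consequence of the assumptions and not as a revised recruitment target.

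If recruitment falls short, judge the need for a modification on pooled events observed, without regard to arm, against 211, and not on the 1,190 head count alone. The text correction needs no new data and changes neither the design nor the analysis. Counting pooled events uses data that are already collected every six months.
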